**Fig. 5 Fig5:**
[figure not shown]
Example photograph of touch-screen icons on e-recording device

### Mechanistic outcomes

#### Anorectal sensorimotor function

Frequency of perceived and unperceived TASRs per unit time (pre- and post-prandial)Anal sensory electrical thresholdRectal volumetric thresholds (minimum, urge, maximum tolerated) to balloon distension

#### Anocortical function

Magnetoencephalography (MEG): recordings will be acquired in response to anal electrical stimulation at 75% pain threshold, voluntary anal squeeze, and to acute supra-sensory sacral-root stimulation. A synchronous anal electromyogram (EMG) will also be recorded to aid interpretation and a control area utilised (median nerve). Whole cortical data will be obtained using standard methods on an Elekta Triux 306 channel system utilising noise cancellation methods to eliminate implant and stimulator artefacts. A beam-former analysis methodology will be employed to evaluate both evoked and induced changes in brain activity associated with SNM and anal stimulation. Brain sources will be constructed using individual co-registered T1-weighted MRI brain volumes. The outcome of this process will be a measure of the changes in brain oscillatory power and/or frequency changes computed from brain structures where maximum changes associated with anal stimulation are observed. These changes will be depicted in statistical brain volumetric images.

### Statistical considerations

#### Sample size

The sample size is based on the primary outcome; i.e. faecal incontinence episodes per unit time as recorded using the 4-week bowel diary at the end of each 16-week crossover phase.

We assume that when the device is inactive, the average number of events in 4 weeks for a typical participant is 28. The number of events per month for that individual will have an over-dispersed Poisson distribution, with 95% range 7 to 112. But individuals will also vary, so the average number of events in a month could vary from 14 in an individual at one extreme to 56 in an individual at the other. This means that the correlation between log(number of events) for the same individual in two different months will be 0.2, and the standard deviation of log(number of events) for each month will be 0.775 (this is consistent with results from two previous NIHR trials in similar populations [18, 34], and with our clinical experience). Thus, to detect a 30% reduction in FI event rate with 90% power at the 5% significance level with a crossover design requires 80 participants. Allowing for 10% loss to follow-up a total of 90 participants will be randomised. This sample size would also achieve more than 90% power to detect a 50% reduction in FI event rate using the data from the first period of the crossover alone. This sample is also sufficient to detect changes in mechanistic outcomes (90% power) based on pilot data; i.e. using a one-sample test comparing logarithm of anal electrical sensitivity post-SNM, the proposed mechanistic sample size *n* = 25 will be sufficient to detect a 30% reduction in sensory threshold with 95% power at the 5% significance level, assuming the standard deviation of the change in log-sensitivity is 0.47 (consistent with a coefficient of variation of 0.5 for sensitivity, as observed in pilot data, and a correlation of 0.5 between pre- and post-SNM assessments). The anocortical studies are mainly exploratory and sample size will be based on success of recruitment. It is, however, envisaged that approximately 15 patients will complete all three visits for MRI/MEG. Previous MEG studies have drawn important conclusions with sample sizes of this order.

#### Method of analysis

##### Efficacy: primary analysis from crossover study

This analysis will be completed by the statisticians at PCTU.

The analysis of the primary outcome will compare SHAM and active therapy in both arms of the crossover trial, at T12–T16 and T28–32, using mixed Poisson regression analysis to adjust for a fixed effect of period and a random effect of individual. To allow observed numbers of events before and after activation in the same individual to have an over-dispersed Poisson distribution we will also include a random effect of time within individual. We will analyse all non-missing data, adjusting for the stratification variables (random effect of centre and fixed effect of sex). This approach is unbiased if missingness is related to observed outcome data or stratification factors from the same participant (a ‘missing at random’ assumption): further sensitivity analyses will explore this assumption if needed.

Secondary outcomes will be analysed in the same way – using Poisson regression for outcomes that are counts, and linear regression for other quantitative outcomes.

Exploratory analyses may also be performed using geospatial data from the touch-screen devices to calculate, e.g. number of outings from primary residence, as well as distance travelled and velocity (a surrogate for mode of transport), and to produce numerical and graphical summaries aggregated by trial arm.

##### Efficacy secondary analysis from cohort study

As in the primary efficacy analysis, mixed Poisson regression will be used to compare the primary outcome at T52–58 with baseline in all randomised participants, adjusting for a random effect of individual, and a random effect of time within individual (over-dispersion).

#### Mechanism studies

Data from the subset of patients undergoing advanced anorectal studies (*n* = 25 approx) will be collected during each phase of the crossover. These data take the form of counts, e.g. number of events, and continuous measures such as pressure. Data will be analysed as for secondary outcomes in the efficacy analysis.

Anocortical studies will be analysed by the Aston Brain institute using existing bespoke computer analysis packages (Graph (Elekta TM); Matlab TM and FieldTrip TM and SPM8 TM). A beam-former analysis methodology [35] will be employed to evaluate both evoked and induced changes in brain activity associated with SNM and anal stimulation. Group analysis of this data will allow determination of cortical reorganisational changes associated with chronic SNM. This will be achieved by the spatial normalisation of individual MRI volumes into a grid based on the Montreal Neurologic Institute (MNI) standard template. Statistical analysis will employ a non-parametric cluster-based permutation test^57^. Firstly, an uncorrected dependent-samples *t* test will be performed on pre- and post-stimulus brain activity across the entire brain volume. All voxels exceeding a 5% significance threshold will be grouped into clusters. A null distribution will be obtained by randomising the condition label (pre- or post-stimulus data) 1000 times and calculating the largest cluster-level *t* value for each permutation. This methodology has been shown to adequately control for issues of multiple comparisons.

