#### Mechanistic objectives

To determine the effect of sub-sensory SNM on anorectal sensorimotor reflex functionHypotheses: (1) SNM but not SHAM increases frequencies of fasting and fed perceived and unperceived transient anal sphincter relaxations (TASR) (based on prolonged high-resolution anorectal manometry recordings) to levels observed in healthy individuals; (2) SNM but not SHAM increases conscious sensation of defaecatory urge based on symptom reporting and objective measures of anorectal sensory functionTo determine the effect of SNM on anocortical afferent functionHypothesis: SNM leads to brain plasticity (based on magnetoencephalography (MEG)) in motor and non-motor cortical and sub-cortical regions

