#### Anocortical studies

Patients in the Midlands area (Sandwell and West Birmingham NHS, University Hospital Birmingham, Heart of England NHS and University of Leicester NHS Trusts) will be identified as potential subjects and provided with the specific PIS. Interested patients will need to make a total of three visits to the Aston Brain Centre.

Only patients known to be proceeding to implantation will be invited for baseline evaluation and this can only proceed after removal of the test electrode (due to magnetic resonance imaging (MRI)) or in those in whom there is good certainty that a tined lead evaluation will progress to implantation. A baseline MEG will be acquired according to the specific protocol developed and tested by the applicants (see Fig. 3). At the same visit (but after the MEG) they will have an MRI head scan. At the second and third visits (SNM or SHAM in random sequence), the patient will have further MEG acquisitions only.

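### The only MEG test specified permutes pre- and post-stimulus labels, so it tests response to the in-session stimulus and, as written, not the SNM plasticity hypothesis

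*Protocol article*

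**What the plan says.** The Mechanistic objectives section of the protocol article gives the MEG hypothesis: "SNM leads to brain plasticity (based on magnetoencephalography (MEG)) in motor and non-motor cortical and sub-cortical regions". The Abstract describes the same aim as a change in how cortical and subcortical regions respond when the anorectum is electrically stimulated.

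The data come from three visits. The Anocortical studies section has a baseline MEG before implantation, and then: "At the second and third visits (SNM or SHAM in random sequence), the patient will have further MEG acquisitions only". Within each session, according to Anocortical function, "recordings will be acquired in response to anal electrical stimulation at 75% pain threshold, voluntary anal squeeze, and to acute supra-sensory sacral-root stimulation".

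The analysis is in the second paragraph of Mechanism studies. It announces its purpose: "Group analysis of this data will allow determination of cortical reorganisational changes associated with chronic SNM". It then describes one test, an uncorrected dependent-samples t "test will be performed on pre- and post-stimulus brain activity across the entire brain volume". Next, "All voxels exceeding a 5% significance threshold will be grouped into clusters". The reference distribution is fixed as follows: "A null distribution will be obtained by randomising the condition label (pre- or post-stimulus data) 1000 times", keeping the largest cluster-level t each time. The paragraph ends by stating that this deals with multiple comparisons.

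The Sample size section calls the anocortical studies mainly exploratory and expects about 15 patients to complete all three visits.

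**The concern.** A plasticity hypothesis concerns a difference between treatment conditions: is the response to the stimulus different under SNM from the response under SHAM? The label that is shuffled decides which null a permutation test addresses. Here it is the stimulus label, so the null is that activity is the same before and after the stimulus. The treatment label appears nowhere in the test.

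The SNM versus SHAM comparison is the only randomised comparison that the MEG data offer. As written, it has no stated test, while the paragraph's conclusion concerns SNM. Running the stimulus test separately in each phase and noting where one map is significant and the other is not would not fill the gap, because that does not test the difference. The multiplicity control described is sound, but it protects the stimulus null.

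**Working it through.** The plan gives no MEG power or error rate to reproduce, so the check is of which null the written test addresses.

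**1. The two nulls.** For participant *i* in a given phase, let D be the post-minus-pre stimulus change at a voxel. Write m for the mean response under SHAM and τ for the change in that response due to SNM.

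| Analysis | Mean tested | No SNM effect (m = 1.5, τ = 0) | SNM doubles response (m = 1.5, τ = 1.5) |
|---|---|---|---|
| Pre/post label, SHAM session | m | 1.5 | 1.5 |
| Pre/post label, SNM session | m + τ | 1.5 | 3.0 |
| Pre/post label, sessions pooled | m + τ/2 | 1.5 | 2.25 |
| SNM minus SHAM difference of D | τ | 0 | 1.5 |

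The first three means are non-zero in both columns. Only the last is zero exactly when SNM has no effect.

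**2. Simulation of the written procedure.** From the plan: 15 completers, a 5% cluster-forming threshold, the largest cluster-level t, and 1000 permutations. Assumed, because the plan gives no figures: a two-sided threshold; 60 voxels on a line, of which 10 respond; noise SD 1, smoothed over three neighbouring voxels; between-participant response SD 0.5; mean responses as in the table; no period effect. There were 500 simulated trials per scenario. The last row swaps SNM/SHAM labels within participant.

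| Rejection rate | No stimulus response | Same response, no SNM effect | SNM doubles response |
|---|---|---|---|
| Pre/post, SNM session | 5.6% | 100% | 100% |
| Pre/post, SHAM session | 5.4% | 100% | 100% |
| Pre/post, pooled | 6.0% | 100% | 100% |
| SNM minus SHAM | 4.2% | 3.8% | 100% |

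The simulation error around 5% is √(0.05 × 0.95 / 500) = 0.0097, so two standard errors span about 3.1% to 6.9%. Every rate that should be 5% lies inside that span. The written test is therefore a valid test of stimulus response, but its result is the same with and without an SNM effect. The 100% figures depend on the assumed response size; the mismatch of nulls does not.

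**3. Period effect.** Let π be the period 1 minus period 2 difference, and assume no carryover. The SNM minus SHAM difference has mean τ + π in the SNM/SHAM sequence and τ − π in the SHAM/SNM sequence. Its plain average is τ + π(n₁ − n₂)/n. With 15 completers split 8 and 7, the bias is π/15; split 10 and 5, it is 5π/15 = π/3.

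The period 1 minus period 2 differences have means π + τ and π − τ in the two sequences. Half the difference between the sequence means is τ, and π cancels. Permuting sequence labels on these differences therefore tests τ and allows for period.

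**4. Number of permutations.** Free within-participant swaps number 2¹⁵ = 32,768. Permuting sequence labels with an 8/7 split gives 15!/(8! × 7!) = 6,435 arrangements; a 10/5 split gives 15!/(10! × 5!) = 3,003. Drawing 1000 at random remains workable in each case.

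**The case against.** The best defence is that the stimulus test has another job. Anocortical function says the outcome measure is computed from the structures that change most with anal stimulation, so the stimulus response serves to find regions, and a pre/post permutation test with cluster correction suits that. The test is also introduced as a first step with no second step following, which suggests abridgement. A journal article may leave a second-level contrast to a fuller plan.

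The localising role stands, and the fix keeps it. But Anocortical function names no SNM contrast either. The article does more than leave detail out: it fixes the statistic, threshold, permuted label and number of permutations, in a paragraph whose stated purpose is to determine SNM-related reorganisation. The sentence that sends data to the secondary-outcome methods belongs to the anorectal paragraph, on counts and pressures, and does not cover MEG.

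It might be said that pre- and post-stimulus means before and after chronic SNM. The recordings are described as responses to stimuli given in the session, and the paragraph calls the therapy chronic SNM, so this does not fit. That reading would also leave out the SHAM comparison.

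It is also fair that the MEG hypothesis, unlike the anorectal ones, does not mention SHAM, and that baseline MEG exists. SNM versus baseline would address the wording, but it is not randomised and is confounded with time and implantation.

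A reader might infer that a significant pre/post cluster will itself be reported as plasticity, with an uncontrolled false-positive rate for SNM. The document never says so, and the simulation cannot show that anyone intends it.

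**Conclusion.** The point holds for the test as written: it addresses response to the in-session stimulus, and the hypothesis that SNM changes brain activity has no stated test. This follows from the permuted label alone. The simulated rates illustrate it and rest on the assumed effect sizes, and the simulated SNM minus SHAM test used free label swaps with no period effect.

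Severity is moderate. The MEG work is mainly exploratory, expects about 15 completers and claims no power. The primary outcome, the other secondary outcomes and the anorectal analyses are untouched. It would go too far to say that the MEG study cannot answer its question, since the SNM and SHAM sessions supply the data needed.

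**What to change.** In Mechanism studies, separate two analyses.

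1. **Localisation.** Keep the pre/post-stimulus cluster test to identify responsive regions, in line with Anocortical function, and say that this is its only role.
2. **Plasticity.** Compute each participant's post-minus-pre map in each crossover phase, and test the within-participant SNM minus SHAM difference with the same max-cluster correction. Build the null by permuting SNM/SHAM order in line with the randomised sequence, that is, by permuting sequence labels on the period differences, so that a period effect is allowed for. Report the number of completers per sequence.

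Label SNM versus baseline as supportive only. Fix this before the MEG data are analysed by condition.

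The cost is a change of wording and some extra analysis of data already planned, with no new visits. There may be fewer significant MEG findings, because a difference between phases is harder to show than a response to a stimulus.

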### Confidentiality

Information related to participants will be kept confidential and managed in accordance with the Data Protection Act 1998, The Data Protection Directive 95/46/EC, NHS Caldecott Principles, The Research Governance Framework for Health and Social Care, ICH Good Clinical Practice Guidelines (1996) and the conditions of Research Ethics Committee Approval and current local regulatory requirements.

All CRFs will be pseudonymised. The participant’s will consent to their general practitioner (GP) and or referring clinician to be informed of their participation in the study.

### Access to data and archiving

The trial data will be made available to suitably qualified members of the research team, study monitors and auditors, the REC and regulatory authorities as far as required by law. When the research trial is complete, it is a requirement of the Research Governance Framework and Sponsor Policy that the records are kept for a minimum period of 20 years (as per sponsor requirements).

### Adverse events (AEs)

All AEs will be recorded on the CRF and in the medical notes. Severity, causality (relationship to study procedures) and assessment of seriousness will be at the discretion of the medically qualified individual (e.g. principal investigator or delegated member of team).

### Expected events

Expected AEs includeBleedingPainWound infectionWorsening of, or de novo urinary incontinenceWorsening faecal incontinenceUnwanted/undesirable stimulation effectsNumbness at neurotransmitter siteTechnical device issues including lead migration and fracture

Expected serious adverse events (SAEs) are those related to routine use of SNM. These are:Infection of lead or implantable pulse generator (IPG) necessitating removal or admission for intravenously administered antibioticsUnwanted stimulation effects necessitating device removalLack/loss of efficacy necessitating device removalRevision of IPG placement due to discomfort or displacementRevision or removal of IPG due to technical device failure (including fractured lead or failure of impedance check on all four leads)Unrelated hospitalisation; e.g. elective surgical procedures or injury or acute medical problems

### Notification and reporting of SAEs

SAEs that are considered to be ‘related’ and ‘unexpected’ are to be reported to the sponsor within 24 h of learning of the event and to the Main REC within 15 days in line with the required timeframe.

### Monitoring and auditing

The PCTU quality assurance manager will conduct a study risk assessment in collaboration with the CI. Based on the risk assessment, an appropriate study monitoring and auditing plan will be produced according to PCTU SOPs. This monitoring plan will be discussed and authorised by the sponsor before implementation. Any changes to the monitoring plan must be agreed by the PCTU quality assurance manager and the sponsor. Audits may be conducted by the sponsor or funder representative. The study may be identified for audit via the risk assessment process, investigator or department request, allegation of research misconduct or fraud or a suspected breach of regulations or selected at random.

### Trial committees

The project will be under the auspices of the chief investigator and the PCTU. The project will be overseen by a Trial Steering Committee (TSC). The role of the TSC is to provide overall supervision of the study on behalf of the sponsor and funder to ensure the study is conducted in accordance with the principles of Good Clinical Practice (GCP) and relevant regulations.

The responsibilities of the TSC will include: ensuring that views of users and carers are taken into consideration; advising on the trial protocol; advising on changes in the protocol based on considerations of feasibility and practicability; assist in resolving problems brought to it by the Trial Management Group (TMG); monitor the progress of the trial and adherence to protocol and milestones; consider new information of relevance from other sources; consider and act on the recommendations of the Data Monitoring and Ethics Committee (DMEC), sponsor and/or REC; review trial reports and papers for publication.

A Trial Management Group (TMG) will meet monthly initially during study set-up and then less frequently, every 2 months. The TMG will be responsible for day-to-day project delivery across participating centres, and will report to the TSC.

A Data Monitoring and Ethics Committee (DMEC) will be convened. The DMEC will meet at least 4 weeks prior to the TSC to enable recommendations to be fed forward. The DMEC will review unblinded comparative data, monitor these data and make recommendations to the TSC on whether there are any ethical or safety reasons why the trial should not continue. The DMEC membership will be in accordance with NIHR/MRC as well as PCTU guidelines.

### Risks / benefits

#### Efficacy study-related risks

The study poses no major risk to participants above the standard risk of SNM therapy. SNM is an established therapy whose main attraction is non-invasiveness and safety compared to other surgical procedures. The short period (3 months) without active therapy imposed by the crossover design is not deemed ‘harmful’ for a chronic and stable condition by the time that surgical intervention is considered. The main procedural risks are unwanted stimulation effects: muscle spasms, vaginal pain, scrotal pain, leg pain and paraesthesia (common to some degree but manageable usually by reprogramming), infection (cited at 2%) and leading to device erosion or removal. Other listed AEs (based on FDA: PMA P080025) include: unwanted changes in bladder function (urgency, retention); pain at neurostimulator and/or lead site including skin irritation; and allergic or immune system response to the implanted materials that could result in device rejections. Malfunction of the components of the InterStim Therapy System including neurostimulator programming error, lead migration/dislodgement, lead fracture, erosion of the lead into the colon with perforation, neurostimulator battery depletion, extension fracture, neurostimulator migration can also occur.

Taking the average natural background radiation in the UK to be 2.3 mSv per annum, then an effective dose of 1.6 mSv for this study is approximately equal to 8 months of natural background radiation exposure. X-ray examination involves exposure to ionising radiation and carries a risk of induction of excess cancers which may not be expressed for many years after exposure. Using the adult population lifetime risk coefficient of 5% per Sievert gives a lifetime risk of cancer of approximately 1 in 12,500. The Public Health England Radiation Protection Division describes risks of this magnitude as very low.

Some of the questionnaires contain personal questions about bowel problems and the effect of these on quality of life and psycho-behavioural functioning; however, all have been used in studies of similar patients previously.

